#### **14.5 Evaluation Methods**

- Perform analyses on adverse events reported by subjects or identified by secondary review to assess the severity and type of adverse events and the incidence of adverse events in the study and control groups.

#### **14.6 Reporting adverse events**

- 1) Severity of adverse events: Allows you to indicate mild, moderate, severe, etc. in the adverse event report card.
- 2) Causality with an investigational medical device: Determine causality based on the evaluation criteria and display it in the adverse event record table.
- 3) Treatment: Allows you to display in the record table if there is a change in the clinical trial method, such as a change in the method of use, a decrease in the number of uses, or a discontinuation of use due to an adverse event.
- 4) Treatment course: Allows you to describe the disappearance or worsening of an adverse event due to treatment after the event occurred.
- 5) Investigator's view: Allows you to record the investigator's view of an adverse event.

**14.7 Reporting method:** This information is reported in accordance with the regulations on medical device clinical trials and the standard work instructions prescribed by the medical device clinical trial center.

- 1) An adverse event is any unintended symptom, manifestation, or disease that occurs in a subject during a clinical trial, and should be recorded in the case report based on the medical findings and severity of the adverse event and the evaluation of the causal relationship with the investigational medical device. Therefore, the criteria for evaluating the causal relationship between an adverse event and an investigational medical device should be presented.

- 2) Safety criteria refers to the criteria for assessing the severity of predicted adverse events and adverse events as they should be assessed and recorded in the case record.
- 3) Safety evaluation methods are statistical analysis methods and evaluators for the comparative evaluation of adverse events, adverse medical events, and the frequency of adverse events associated with investigational medical devices between test and control groups.

Presented quasi-.

- 4) Adverse Event Reporting: The Principal Investigator must promptly notify the Sponsor of all serious adverse events and make a detailed, documented follow-up report in accordance with the protocol. In the case of a fatal or life-threatening event, a further report must be made to the sponsor within 7 days of the date the sponsor receives or learns of the event, in which case detailed information about the adverse event must be provided within 8 days of the initial report. In the case of other serious and unexpected adverse medical events, the sponsor must report each to the head of the Ministry of Food and Drug Safety within 15 days of the date the sponsor receives or learns of the event.

## **15 Informed consent form (attached)**

## **16 Victim compensation protocols**

In the event of any damage or harm related to this clinical trial, **the clinical trial sponsor (Link Optics Co., Ltd.)** will take **full legal responsibility and compensate** for the **damage**, and **side effects and worsening of the disease** will be **treated with known treatment methods**. However, **other injury-related or disease-related expenses such as lost wages will not be compensated.** **The study physician and research staff will provide you with additional information about all other possible financial compensation.**

temporary pain or damage that can be easily treated, and the site determines that treatment is necessary (coverage is limited to the cost of the necessary treatment).

You need to be hospitalized or have your hospital stay extended.

Causes persistent or significant disfigurement or diminished donation.

④ Causes birth defects or abnormalities

Causes death or threatens life.

### **16.1 Reward requirements**

Subject compensation under this Compensation Agreement is subject to the following requirements

Physical injury caused by the investigational clinical device.

The subject's condition has worsened as a result of the clinical trial.

③ The investigator has complied with all aspects of the protocol approved by the Korea Food and Drug Administration.

- ④ was not caused by the tester's manifest negligence or dereliction of duty; and
- The subject has complied with all instructions given by the principal investigator or study staff.
- ⑥ The subject has taken steps to minimize the incidence of damages resulting from the  
bodily injury.

## 16.2. Reasons for Exclusion

Damage due to insufficient effectiveness, efficacy expected from an  
investigational clinical medical device

Skin wrinkles and skin elasticity do not improve with the use of this clinical  
device.

Damage caused by the subject's negligence

If it hasn't been used on a given body part for a given amount of time.

: Failure to seek counseling and medical attention in the event of an adverse event.

Failure to comply with subject precautions.

## < Note to subjects

- 1) People with photosensitivity should not use it.
- 2) Use caution when combining medications and foods that increase photosensitivity as they may cause damage, such as burns, to the area where the device is used.
  - Drugs known to cause photosensitization : Quinolones (nalidixic acid, ofloxacin, sparfloxacin, etc.), tetracyclines (minocycline hydrochloride, doxycycline hydrochloride, etc.), sulfa drugs, griseofulvin, tar preparations, ciclosporins (etsiagit, cyclobenzazid, fenfluthizide, etc.), porphyrins (NAPP, etc.), phenothiazines (prochlorperazine, chlorpromazine, etc.), methylene blue, etc.
  - Foods that increase photosensitivity  
: Foods containing furocoumarin (celery, lime, carrots, parsley, figs, mustard, etc.)
- 3) Not for use by pregnant or lactating women.
- 4) Do not expose the product to excessive humidity, overheating, or overcooling.
- 5) Do not use the product when it is wet or leaking water.
- 6) The product will overheat and should not be used continuously for more than 30 minutes.
- 7) If the light irradiator is heavily contaminated, the product efficiency will be reduced, so decontaminate it with a dry towel before use.
- 8) When the product is in operation, the patient should not look at the illuminated light source with their eyes.

9) It should not be used on open wounds.

- 10) To prevent electrical shock, store away from contact with magnets or energized objects.
- 11) You may not modify, disassemble, or repair the product in any way.
- 12) If you feel uncomfortable while using the product, stop using it.

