## 6.2 Purpose of Use and Prior Research

### 6.2.1 Purpose of use (indications)

It is used to treat skin diseases, treat pressure ulcers, and relieve pain by irradiating the affected area with visible and infrared light.

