### **7.1 Subject's selection criteria**

- (1) Patients with stage 2 pressure ulcers (based on NPUAP guidelines) in the hip area.
- (2) 13 years of age or older

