## 9 Clinical Trial Methods

### 9.1 Designing a clinical trial

For subjects who signed the informed consent form of their own volition, after conducting the necessary examinations and tests according to the protocol, reviewing the inclusion and exclusion criteria, and deeming them suitable for this study, educating them about the study schedule and methods. The subjects will be **irradiated with 4 wavelengths of LEDs at maximum power (5 levels,  mW/cm^2) for maximum time (25 minutes) at a distance of 15 cm from the pressure ulcer in the buttock area. LED irradiation is performed 3 times per week, with a medical examination and wound assessment at the end of each week's treatment. This is done for a total of 4 weeks.**

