#### 9.3.2 Application and duration of use

- **Site of application:** pressure ulcer on subject's hip area
- **Runtime:** 4 wavelengths of LEDs (460 nm : BLUE, 595 nm : AMBER, 630 nm : RED, 850 nm : NIR)  
irradiated for the maximum time (25 minutes) at full power (5 steps, 90 mW/cm^2 ).
- **Sham device:** 25 minutes, just like the experimental group. For details on how to use the sham device, see As described in 9.3.6.

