#### **10.3.2 Visit 2 (D1 ± 2 days)**

Recheck the selection criteria and exclusion criteria before irradiation, then judge the suitability and assign the subject number.

Medical examination and measurement of vital signs

Measures area assessment, Braden scale, and NRS

- ④ Phototherapy performed.
  - ⑤ Performed bacterial identification and histologic examination
- Checked medical history and medications.
- ⑦ Check for adverse events.

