## **13 Evaluation criteria, methods, and interpretation of validity (based on statistical methods)**

### **13.1 Primary efficacy measures: wound size and degree of re-epithelialization**

- Wound size and degree of re-epithelialization in the control and experimental groups at 0 and 4 weeks were plotted against time, respectively, and differences between the two groups were analyzed using a paired t-test.
- Wound size and degree of re-epithelialization will be measured by the investigator on the day of the study visit by physically examining the pressure ulcer size (width × length × depth: measured in cm using a ruler). Photographs of the treated area will be taken, including a 1 cm X 1 cm grid at the time of measurement.

\*How to take clinical photographs: At the time of each visit, photographs should be taken at a 90° angle and at a distance of 15 cm, using the camera in use in the clinic. For consistent evaluation, ensure that the photographs are taken under the

same conditions (angle, same camera, etc.).

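### Minor: the Note to subjects bars the device on open wounds, yet the protocol directs it at a stage 2 ulcer that it assesses as one; the topical rules also differ

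*Protocol*

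**What the plan says.** Item 9 of the Note to subjects reads "It should not be used on open wounds". The Note follows directly on section 16.2, whose list of reasons to exclude compensation includes "Failure to comply with subject precautions".

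The treatment sections point the other way:

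- Section 7.1 requires "Patients with stage 2 pressure ulcers (based on NPUAP guidelines) in the hip area".
- Section 9.1 sets the light "at a distance of 15 cm from the pressure ulcer in the buttock area", three times a week for four weeks.
- Section 9.3.2 gives the site of application as "pressure ulcer on subject's hip area".
- Section 6.2.1 states of the device: "It is used to treat skin diseases, treat pressure ulcers, and relieve pain".

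On wound care, section 9.2.1 step 4 calls for an antibacterial ointment after each irradiation, names three products and leaves the list open. Section 9.3.7 prescribes daily 1% silver sulfadiazine plus foam for everyone in both arms. In principle it also prohibits other medicines that may affect efficacy; unavoidable exceptions are to be recorded.

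**The concern.** A subject who reads the Note is told not to allow what the protocol then does to him or her. Because the Note is the natural referent of the precautions named in section 16.2, the contradiction also touches the compensation terms. Section 16.1 adds to this, since it makes compensation depend on the subject having followed the instructions of the investigator and staff. Read literally, a subject with an open ulcer who accepts irradiation follows the staff but not item 9, and one who refuses follows item 9 but not the staff.

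The topical question is separate and smaller. An ointment other than silver sulfadiazine is ordinary care under section 9.2.1 but could be read as a restricted medicine under section 9.3.7, and nothing says which section governs. Background wound care bears on a wound-size endpoint, so staff and monitors need one rule by which to judge deviations.

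**Working it through.** No arithmetic applies: the point is one of text, and no figure in the protocol enters it. The check is to set the sections side by side.

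**1. Is the irradiated ulcer an open wound in the protocol's own terms?** The protocol never uses that label for a stage 2 ulcer, so this has to be inferred.
- Section 5.2 says that stage 2 shows skin damage.
- Section 10.2 has the investigator assess depth, discharge, bleeding and granulation tissue.
- Section 13.1 measures width, length and depth and makes re-epithelialization a primary measure: "Wound size and degree of re-epithelialization will be measured by the investigator on the day of the study visit".
- Section 9.2.1 orders a session as saline cleaning, light, saline cleaning, ointment, dressing. The ulcer is therefore undressed while irradiated.

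A lesion with depth, discharge and granulation, scored on how far the epithelium has grown back, is naturally read as open.

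**2. Is it still there when treatment starts?** Section 10.3.2 has staff "Recheck the selection criteria and exclusion criteria before irradiation" at Visit 2. A subject first irradiated at that visit therefore still has the qualifying ulcer.

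**3. Does any text exempt the study ulcer from item 9?** None was found. Section 6.2.1 names pressure ulcers as an intended use, but it neither refers to item 9 nor limits it.

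**4. Does item 9 look like a considered device warning?** The text at hand does not settle this. Neither the cautions in section 9.3.5 nor those in section 11.2 repeat the bar. Section 16.2 also mentions skin wrinkles and elasticity, which have no place in a pressure ulcer trial and suggest text carried over from another use.

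**5. How strong is the link to compensation?** Weak.
- The line on precautions comes under damage caused by the subject's own negligence.
- Section 9.3.5 lets only authorised and medical personnel operate the device.
- A subject who attends sessions run by staff meets the section 16.1 condition on following instructions.
- Sections 16, 16.5 and 17 all lean towards cover.

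**6. Do the two topical rules exclude each other?** No. If the ointment chosen is silver sulfadiazine and the dressing is foam, both sections are met. They differ in that one leaves the agent open and the other fixes it.

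**7. Can the topical rule simply be settled on silver sulfadiazine?** Not without a check. Item 2 of the same Note lists sulfa drugs among agents known to cause photosensitization, and exclusion criterion 8 in section 7.2 excludes people taking light-related medication. The protocol does not say whether topical silver sulfadiazine falls under either.

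**The case against.** The strongest reply is that nobody would be misled. Pressure ulcers are a stated use, sections 7 to 9 are unambiguous, staff operate the device, and no investigator would withhold treatment because of a line attached to the compensation terms. The protocol also never calls the ulcer open, and the consent form, which might word the matter differently, is a separate attachment that is not at hand. Most of this stands, and it is why the point is minor. It does not remove the contradiction: item 9 is current text, is addressed to subjects and has no exception.

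On the topicals, the two sections can be read as a general and a specific statement of the same care, and ointments that the protocol itself directs are hardly foreign medicines. That is fair. What remains is an open list beside a fixed regimen.

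Four stronger readings are tempting, and the documents support none of them.

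- **Subjects stand to lose cover.** The sections listed in step 5 of the working make this unlikely.
- **Subjects are exposed to a known hazard.** The protocol gives no reason for item 9, and section 6.2.1 lists the use as intended. Only the sponsor can say whether a device risk lies behind it.
- **The number of conflicting sessions can be counted.** The protocol does not say when an ulcer stops being open. The recovery time of 1 to 3 months for mild cases in section 5.2 has no stated starting point and is longer than the treatment period, whose last regular session in the section 10.1 table is on D26.
- **The topical difference biases the comparison.** Section 9.3.7 applies to both arms, and nothing suggests that ointment choice would differ between them.

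**Conclusion.** The concern holds as a minor internal inconsistency. Item 9 is wrong as written for this trial, because the protocol requires irradiation of an ulcer that its own assessments describe as an open wound. The compensation line makes the wording worth correcting, but the practical risk from it is slight. The topical mismatch is real and secondary.

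No endpoint, sample size or error rate changes. The conclusion rests on two inferences: that a stage 2 ulcer assessed as in sections 10.2 and 13.1 is an open wound, and that the precautions in section 16.2 are those in the Note that follows. Should the sponsor find that item 9 reflects a genuine device risk, the matter would be more serious than a wording error, but nothing in the protocol shows that.

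**What to change.** 1. The sponsor confirms whether item 9 reflects a real device risk or is carry-over text. This comes first, because the change relaxes a device warning.
2. If no risk stands behind it, delete item 9 or qualify it so that it does not apply to the study ulcer irradiated as the protocol directs.
3. State in section 16.2 that treatment given as directed by the protocol is not a ground to refuse compensation.
4. Align section 9.2.1 step 4 with the single daily regimen that section 9.3.7 already fixes for both arms, and name any permitted alternatives. Before doing so, check silver sulfadiazine against item 2 of the Note and exclusion criterion 8. The choice of agent remains a clinical one for the sponsor and the investigator.

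The cost is wording in the protocol and subject information, plus IRB handling. No visit or test is added. Clinicians' choice of ointment narrows slightly.

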### **16.3 Reward criteria**

If there is a pre-agreed compensation amount or measure between the parties for an anticipated medical device adverse event, we will compensate according to that standard.

In other cases, compensation shall be provided in accordance with the compensation method agreed upon between the parties, taking into account the extent, nature, duration, and similar cases of physical damage.

③ If the parties do not agree on the preceding paragraph, compensation shall be provided in accordance with the court's judgment and the confirmation of the corresponding decision.

### **16.4 Compensation Process**

Subjects who suffer bodily injury under this Compensation Policy should contact the principal investigator of the clinical trial or the clinical trial center for necessary medical treatment.

Subjects whose physical injuries are not cured despite the actions of the principal investigator or the institution may request compensation from the sponsoring organization.

③ After receiving the above compensation request, the sponsoring organization shall promptly investigate whether the compensation is applicable and the compensation standard, and notify the subject about it.

④ The subject must notify the sponsoring organization within five (5) business days from the date of receipt of the above notification of any objections to the above notification.

⑤ If the Subject fails to notify us of any objection after receiving the notice in paragraph (3), the Parties understand that we have agreed to compensation in accordance with the above notice.

⑥ If the subject notifies an objection in accordance with the provisions of Paragraph (4), the sponsoring organization shall recommend multiple objective experts to the subject to determine whether the subject is eligible for the above compensation and the compensation standard, and the subject shall nominate one such expert within three (3) business days from the date of the above recommendation. (If the subject does not nominate, the sponsor shall select one at

random.)

### **16.5 Coverage**

(1) This Compensation Agreement applies to subjects participating in all clinical trials sponsored by the Sponsoring Organization.

unless there is a different arrangement between them.

Any agreement that a subject enters into with any other third party in connection with a clinical trial that is not approved by the Sponsor for compensation for the clinical trial is not enforceable against the Sponsor.

**We take care to ensure that subjects do not suffer any disadvantages as a result of this study, and we pledge to be responsible under the Victim Compensation Policy if any problems arise as a result of this study.**

[figure not shown]

## **17 Post-trial care for subjects**

Patients who drop out of the clinical trial or do not respond shall be instructed to receive other appropriate treatment, and patients whose clinical trial is terminated shall follow the treatment procedures of the hospital for subsequent treatment, and the subsequent treatment costs shall be supported by the subject. However, in the event of an adverse event, after confirming the existence or absence of a causal relationship with the clinical medical device used in the clinical trial, if the adverse event is caused by the clinical medical device used in this clinical trial, the sponsor shall pay for the treatment until the adverse event disappears.

## **18 Research subject risks and benefits**

For mild pressure ulcers, conservative treatment is performed and includes antibiotic therapy and wound disinfection, as well as repositioning to relieve pressure. There are many wound disinfection agents available, but each has its own limitations, and there is no clinically established method of disinfection. If you decide not to participate in this study, you will receive usual conservative care, and you will be able to decline phototherapy even during the study, and you will be able to receive usual conservative care immediately afterwards. Therefore, we will strive for recovery of your condition regardless of whether you participate in the study, and we will try to minimize harm to you.

The expected side effects of the study medical device are increased exudate in the hip area, bacterial growth, wound hemorrhage, tissue necrosis, and pain, microbleeds, and redness with photobiologic therapy.

Side effects may occur. Examples of treating adverse events as soon as they occur

In the event of any injury or damage related to this study, the sponsor (LinkOptics Co., Ltd.) will be solely responsible and will compensate for the damage. However, other injury-related or disease-related expenses, such as lost wages, will not be covered.

The expected benefit of participating in this study is that the study will pay for blood tests, urine tests, radiology tests, biopsies, and bacterial identification tests related to the study while you are participating in the study. You will be responsible for any hospitalization and laboratory fees not related to the conduct of this study.

## **19 Measures to protect the safety of human subjects**

### **19.1 Clinical trial site**

The head of the organization conducting the clinical trial shall ensure that the clinical trial is properly conducted by equipping the clinical laboratory, facilities, and specialized personnel necessary for the conduct of the clinical trial and taking necessary measures in case of emergency.

### **19.2 Institutional Review Board (IRB)**

IRBs should be organized in accordance with national laws, regulations, and practices and should protect the rights, safety, and welfare of human subjects. It should also scrutinize the validity of the reasons for enrolling subjects from vulnerable populations in clinical trials. In fulfilling its duties, the IRB must take necessary measures, such as ordering the principal investigator to stop part or all of the trial, if it finds that the subjects' consent to participate in the trial was not properly obtained, if the trial is not conducted according to the protocol, or if serious adverse events or adverse reactions occur.

